### Interim analyses {21b}

There will be no interim analyses in this trial because the primary outcome is the 5-year all-cause mortality which requires long-term follow-up.

### Methods for additional analyses (e.g., subgroup analyses) {20b}

Three prespecified subgroup analyses of age (18–49 vs. 50–80), gender and body mass index (< 24 vs. ≧ 24) will be conducted for the primary outcome by adding an interaction term (e.g., age × group) into the Cox regression model. A sensitivity analysis will be conducted for the primary outcome based on the per-protocol set, which included patients who adhered to the treatment and follow-ups.

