### Intervention description {11a}

Participants allocated to the experimental group will be admitted to the hospital promptly for the scheduled endovascular repair which will be performed by surgeons with at least 5 years’ experience. After the standard induction of general anesthesia, the invasive arterial blood pressure of the right radial artery will be monitored. Systemic heparinization (1 mg/kg) will be employed before the establishment of the common femoral artery access via which the endografts will be delivered. During the procedure, the end of the frozen elephant trunk will be used as the proximal landing zone, while the descending aorta above the diaphragm will be chosen as the distal landing zone. Endograft selection and coverage length will be largely left to the discretion of the operating surgeons based on imaging measurements. Patients in the experimental group will concurrently undergo conventional antihypertensive treatment as well.

Participants in the control group will not undergo early surgical treatment but will only receive routine antihypertensive therapy.

Follow-up appointments are scheduled at 3, 6, 12, 24, 36, 48, and 60 months after open surgery. An aortic CTA will be required for every follow-up.

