### Outcomes {12}

In this trial, the outcomes will be developed according to the standard clinical endpoint of endovascular aortic repair [17, 18]. The primary outcome will be the 5-year all-cause mortality. Secondary outcomes will include re-intervention (indications for re-intervention: aortic diameter ≥ 55 mm, aortic diameter growth rate > 10 mm/year, or pain or malperfusion symptoms [19]), aortic-related mortality, stroke, paraplegia, renal insufficiency, hepatic insufficiency, extremity ischemia, myocardial infarction, endoleak, graft infection, and graft migration. Other morphological outcomes will include segmental aortic remodeling and the FL thrombosis quotient.

The morphological measurements will be analyzed through three-dimensional reconstruction based on CTA images. The celiac trunk will divide the downstream aorta into two segments. Segment A will be from the end of the frozen elephant trunk to the celiac trunk, and segment B will be from the celiac trunk to the aortic bifurcation. The volume of FL, perfused false lumen (PFL), and true lumen (TL) will be measured for the two segments. The FL thrombosis quotient will be calculated using the formula FL_thrombosis quotient_ = 1-PFL/FL and given as a percentage, and the aortic remodeling will be classified into three types based on volumetric changes [20]. Positive aortic remodeling will be defined as a TL increase of > 10% with a stable FL or a FL decrease of > 10% with a stable TL. Changes within 10% will be considered stable, and all other conditions will be regarded as negative remodeling.

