## Data collection and management

### Plans for assessment and collection of outcomes {18a}

Baseline data will be collected after participants have signed informed consent. For the experimental group, intervention-related data will be obtained from the electronic medical records system within 30 days after patient discharge. Follow-up data will be obtained through outpatient visits or telephone interviews after the participants have completed each follow-up aortic CTA examination.

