### Methods in analysis to handle protocol non-adherence and any statistical methods to handle missing data {20c}

The primary outcome will be analyzed according to the modified intent-to-treat principle, which will minimally exclude patients without receiving the assigned treatment or with missing primary outcome data.

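### The per-protocol sensitivity set selects patients on follow-up attendance after randomisation, which suits a 5-year mortality outcome badly and can mislead if attendance differs by arm

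*Protocol article*

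**What the plan says.** The primary endpoint is fixed in Outcomes {12}: "The primary outcome will be the 5-year all-cause mortality". Under Methods for additional analyses {20b} the article names one robustness check on it: "A sensitivity analysis will be conducted for the primary outcome", "based on the per-protocol set, which included patients who adhered to the treatment and follow-ups". The other analyses in that section are three subgroup interaction tests.

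The follow-ups in question are set out in Intervention description {11a}: "Follow-up appointments are scheduled at 3, 6, 12, 24, 36, 48, and 60 months after open surgery", and "An aortic CTA will be required for every follow-up". That is seven visits. Section {20b} does not say how many may be missed, or how a patient who dies before a later visit is classed.

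The primary analysis set, in section {20c}, is a modified intent-to-treat set that "will minimally exclude patients without receiving the assigned treatment or with missing primary outcome data". On data collection, section {18a} says "Follow-up data will be obtained through outpatient visits or telephone interviews". The rest of that sentence places this contact after each follow-up CTA has been completed.

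**The concern.** A per-protocol set should be defined by things that death does not determine. Attendance over 60 months is not one of them. A patient who dies before month 3 has no visit to miss, while a survivor has seven. Any rule that penalises missed visits therefore sorts patients partly by the outcome.

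The rule is also unnecessary. The Kaplan–Meier, log-rank and Cox methods in section {20a} use partial follow-up through censoring, so a patient who misses a CTA need not leave the analysis.

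What is at stake is the value of the check. If it agrees with the primary result, it adds little, because its set lies inside the primary set. Adherence to treatment implies having received it, and a patient with unknown 5-year status can hardly have adhered to follow-up. If it disagrees, the reader cannot tell whether treatment adherence or visit attendance is the cause. In an open-label trial where only one arm has had a new procedure, attendance may differ between arms, and a treatment effect could then appear or disappear for that reason alone.

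**Working it through.** **Inputs from the article.** 5-year mortality 11.0% (TEVAR) and 29.8% (control), and N = 154 at 1:1, from Sample size {14}; seven visits at 3, 6, 12, 24, 36, 48 and 60 months, from {11a}.

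**The plan's own figure.** Unpooled two-proportion formula, two-sided 5%, 80% power: n = (1.960 + 0.842)² × (0.110×0.890 + 0.298×0.702) / 0.188² = 7.85 × 0.3071 / 0.03534 ≈ 68.2, so 69 per arm. Then 69/0.9 = 76.7, so 77 per arm and 154 in total. The stated size reproduces, and this point does not affect it.

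**Assumptions (not in the article).** Constant hazard from month 1.5 to month 60; each due visit missed independently with probability m; a patient stays in the set only if every visit due while alive was attended. The range for m is 1.5% to 10%. The low end is chosen because 1 − 0.985⁷ = 10.0% of survivors would then be excluded, which matches the 10% dropout in {14}, the only related figure given.

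**Formulas.** With d_k the probability of dying after k visits (k = 0 to 6) and S the 5-year survival:
- deaths kept D = Σ d_k(1 − m)^k
- survivors kept V = S(1 − m)⁷
- mortality in the set = D/(D + V)
- hazard ratio = ln(1 − mortality in TEVAR) / ln(1 − mortality in control)

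**Worked case, control arm, m = 5%.** d_k = 0.0090, 0.0178, 0.0347, 0.0657, 0.0611, 0.0568, 0.0528. D = 0.2462. V = 0.702 × 0.95⁷ = 0.702 × 0.6983 = 0.4902. Mortality = 0.2462/0.7364 = 33.4%, with 74% of patients kept. The same steps for TEVAR give 0.0904/0.7119 = 12.7%, with 71% kept.

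**Equal attendance in both arms.**

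| Missed per visit | TEVAR mortality | Control mortality | Kept (TEVAR / control) | Hazard ratio |
|---|---|---|---|---|
| 0% | 11.0% | 29.8% | 100% / 100% | 0.329 |
| 1.5% | 11.5% | 30.8% | 90% / 91% | 0.331 |
| 5% | 12.7% | 33.4% | 71% / 74% | 0.334 |
| 10% | 14.8% | 37.7% | 50% / 54% | 0.339 |

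**Unequal attendance, no true effect (29.8% in both arms).**
- 3% missed in TEVAR, 10% in control: 31.9% versus 37.7%, a gap of 5.7 points before rounding. Hazard ratio = ln(0.681)/ln(0.623) ≈ 0.81, with 83% and 54% of patients kept.
- 1.5% versus 3%: 30.8% versus 31.9%, hazard ratio 0.96.
- If TEVAR patients attend worse instead (10% versus 3%), the first result inverts to about 1/0.81 = 1.23.

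**Variant.** Starting the hazard at month 0 changes the equal-attendance mortalities by about 0.3 points at most. In that variant, 2% versus 10% missed with no true effect gives 31.2% versus 38.0%. About 68 and 42 of 77 patients per arm remain, and a two-proportion test favours TEVAR significantly about 11% of the time, against a nominal 2.5%.

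**Strict reading.** If all seven visits are required, D = 0 and mortality is 0% in both arms, so nothing can be analysed.

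**The case against.** The strongest reply is that the article never says one missed CTA removes a patient, or that death counts as non-adherence. Such operational detail is commonly left to the analysis plan, which is not shown. A reader might infer that the sponsor intends to drop every death. The text does not support that: it would empty a mortality analysis, and the wording fits equally well with excluding patients lost to follow-up. The strict reading shows only that the definition fails if taken at face value. The attendance criterion itself is nonetheless stated outright, and it is the wrong kind of criterion under either reading.

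A reader might also infer that the check is badly biased in any event. It is not. With equal attendance the hazard ratio hardly moves, and at 1.5% missed per visit mortality shifts by about 1 point or less. A material distortion needs attendance that differs by arm. The article gives no evidence of that, and section {18b} offers travel allowances and reminders without distinction by arm. An imbalance as large as 3% versus 10% would also show in the numbers kept, 83% against 54%. These points stand and limit the size of the concern.

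It would go too far to say that attendance is the main difference between the two sets. Both arms receive antihypertensive therapy, so adherence to treatment may mean more than having received the assigned treatment.

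Finally, this is a supportive analysis. The primary test and the sample size are untouched, and an unseen analysis plan may contain further checks.

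**Conclusion.** The point holds as a flaw in a stated definition, of moderate weight. The per-protocol set conditions 5-year mortality on attendance after randomisation. It is empty of deaths on a strict reading and removes survivors preferentially on a lenient one.

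Under the assumed constant hazard and independent misses, equal attendance leaves the hazard ratio between 0.331 and 0.339 against 0.329, at the cost of up to half the patients and inflated absolute mortality. Unequal attendance can create a spurious effect, for example a hazard ratio of about 0.81 with no true effect at 3% versus 10% missed, in either direction depending on which arm attends better. The miss rates are assumptions, because the article gives none.

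Separately, and without any assumption about miss rates, a set nested in the modified intent-to-treat set cannot test that set's exclusions. No analysis stated in the article covers all randomised patients. The documents do not support a conclusion that the primary result itself is biased by this rule.

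**What to change.** In section {20b}, delete the follow-up criterion from the per-protocol definition. State that all deaths are kept and that patients who miss visits are censored at the date last known alive.

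That alone is not enough, because a set defined by treatment received would nearly duplicate the modified intent-to-treat set in {20c}. Make the main sensitivity analysis all randomised patients by allocated arm, censored at the date last known alive, and keep the per-protocol analysis as secondary support.

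The cost is a wording change, one further analysis and some extra contact work. Section {18a} ties the planned outpatient or telephone contact to a completed CTA, so it does not clearly reach patients who miss one. Vital status would have to be sought from them by telephone. The change should be made before outcomes are compared by arm.

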### Methods in analysis to handle protocol non-adherence and any statistical methods to handle missing data {20c}

The primary outcome will be analyzed according to the modified intent-to-treat principle, which will minimally exclude patients without receiving the assigned treatment or with missing primary outcome data.

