### Concealment mechanism {16b}

The allocation sequence will be securely stored in sequentially numbered, opaque, sealed envelopes. Once the consent form is completed, the allocation will be revealed to the investigators and participants.

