## Discussion

Type I aortic dissection is still a challenge for cardiovascular surgeons. The frozen elephant trunk has achieved promising early and mid-term outcomes with the purpose of closing the intimal tear at the proximal descending aorta and promoting thrombosis of the false lumen along the stent graft [23, 24]. However, residual tears and continuous perfusion of the FL in the downstream aorta adversely affect the long-term prognosis, which will lead to secondary interventions in downstream segments [7, 8]. Several studies have demonstrated the safety and effectiveness of TEVAR in distal aortic re-interventions after frozen elephant trunk implantation [11–13, 25]. However, these studies were all single-center retrospective research, and endovascular re-interventions were mainly used to address distal aortic aneurysmal dilatation. Another single-center study enrolled 26 patients with dissection extending to the aortic bifurcation and compared downstream aortic remodeling following the standard or the elongated (an additional thoracic stent-graft implanted down to the celiac trunk within 30 days) frozen elephant trunk procedure [26]. It showed that an extra stent-graft appeared to improve aortic remodeling and lower the risk of distal aortic re-interventions. Nonetheless, it is important to note that routine extensive descending aortic coverage with a short interval increases the risk of spinal cord ischemia. Therefore, in our study, TEVAR will be performed at least 30 days after the frozen elephant trunk procedure but within 90 days of the onset to promote collateral revascularization of intercostal arteries and reduce the influence of rigid thick intimal flap on the aortic remodeling. Meanwhile, we will only enroll patients with dominant FL and residual tears in the descending thoracic aorta after the frozen elephant trunk implantation because they will be at higher risk for distal aortic adverse events and negative remodeling. Thus, evaluating early intervention is critical for these patients.

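### The primary mortality analysis excludes randomised patients who did not receive their assigned treatment, which can drop pre-procedure deaths from the TEVAR arm while the same deaths count in control

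*Protocol article*

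**What the plan says.** The section on non-adherence and missing data {20c} names a modified intention-to-treat principle for the primary outcome, "which will minimally exclude patients without receiving the assigned treatment or with missing primary outcome data". Outcomes {12} defines that outcome: "The primary outcome will be the 5-year all-cause mortality".

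Three other sections determine how the rule works in practice:

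- Concealment mechanism {16b}: "Once the consent form is completed, the allocation will be revealed to the investigators and participants".
- Intervention description {11a}, experimental arm: "Participants allocated to the experimental group will be admitted to the hospital promptly for the scheduled endovascular repair". The Discussion adds the window: "TEVAR will be performed at least 30 days after the frozen elephant trunk procedure but within 90 days of the onset".
- Intervention description {11a}, control arm: "Participants in the control group will not undergo early surgical treatment but will only receive routine antihypertensive therapy".

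The additional-analyses section {20b} states one sensitivity analysis for the primary outcome, "based on the per-protocol set, which included patients who adhered to the treatment and follow-ups". Statistical methods {20a} plans Kaplan–Meier curves, a log-rank comparison and a Cox model adjusted for centre.

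**The concern.** The rule is worded the same for both arms, but the arms are not equally exposed to it. After allocation, a TEVAR patient must still survive, stay fit and agree until the procedure takes place. A control patient is already on the assigned therapy and has no procedure to reach. A death or clinical deterioration in the waiting period therefore removes the patient from the TEVAR arm but is counted in control. The groups compared are then no longer the groups randomised, and the difference arises from events related to the primary outcome.

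The trial is unblinded, and section {11b} lets investigators withdraw a patient on safety grounds, so a decision not to proceed is made knowing the arm. The Discussion argues that all-cause mortality is unlikely to be affected by lack of blinding. That holds for how a death is recorded. It does not protect the choice of which patients are counted.

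The per-protocol set cannot reveal the problem, because it also leaves out patients who did not have the assigned procedure.

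**Working it through.** **Inputs from Sample size {14}.** Mortality 11.0% (experimental) and 29.8% (control), two-sided 5% error, 80% power, 69 per group, 10% dropout, 154 in total.

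**Reproducing the plan's figure.** Unpooled two-proportion formula: n = (1.960 + 0.842)² × (0.110×0.890 + 0.298×0.702) / (0.298 − 0.110)² = 7.849 × 0.3071 / 0.03534 = 68.2, rounded up to 69. Then 69/0.9 = 76.7, rounded up to 77 per arm, or 154. The sample size is sound and is not at issue.

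**Bias when there is no true effect.** Let both arms have true 5-year mortality p = 29.8% with 77 randomised to each. Let a share f of the TEVAR arm be excluded as untreated, with mortality q among them. Neither f nor q is in the protocol; both are assumptions.

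- Mortality shown in the TEVAR arm: p* = (p − f·q)/(1 − f).
- Chance of a significant result favouring TEVAR: Φ[(d − 1.96·SE₀)/SE₁], with d = p − p*, SE₀ the pooled and SE₁ the unpooled standard error, and arm sizes 77(1 − f) and 77.

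Example, f = 5%, q = 100%: p* = (0.298 − 0.050)/0.95 = 26.1%; d = 0.0369; SE₀ = 0.0733; SE₁ = 0.0732; Φ[(0.0369 − 0.1437)/0.0732] = Φ(−1.46) = 7.2%.

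**A low anchor from the protocol's own rate.** The TEVAR window leaves a wait of at most about 60 days. Assuming a constant hazard, 29.8% over five years gives −ln(0.702)/5 = 0.0708 per year. Deaths are then 1 − exp(−0.0708×14/365.25) = 0.27% over 14 days and 1.16% over 60 days, that is 0.2 to 0.9 of 77 patients. The early hazard may be higher than a constant hazard implies.

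| Untreated share f | Their mortality q | TEVAR arm reads | False result favouring TEVAR |
|---|---|---|---|
| any | 29.8% (average) | 29.8% | 2.5% |
| 0.27% | 100% | 29.6% | 2.6–2.7% |
| 1.16% | 100% | 29.0% | 3.2% |
| 5% | 60% | 28.2% | 4.0% |
| 10% | 60% | 26.4% | 6.5–6.6% |
| 5% | 100% | 26.1% | 7.2–7.3% |
| 10% | 80% | 24.2% | 11.3–11.5% |

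Where a range is shown, its ends are the formula and a simulation.

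**How few exclusions matter.** Chi-square without continuity correction, 23/77 deaths in control:

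- TEVAR 14/77: χ² = 2.88, p = 0.090. Two pre-procedure deaths dropped, 12/75: χ² = 4.12, p = 0.042.
- TEVAR 15/77: p = 0.135. Three dropped, 12/74: p = 0.047.

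These are chosen near-threshold cases. With the continuity correction the first pair is p = 0.131 and p = 0.066, so the shift remains but the threshold is not crossed.

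**Missing-outcome exclusion.** Suppose every death is known and 10% of survivors lack status. Observed mortality is p/[p + 0.9(1 − p)]: 11.0% becomes 12.1% and 29.8% becomes 32.0%. Both arms move up. With equal mortality and equal loss, no difference is created.

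**The case against.** The strongest reply is that the effect may be close to nil. Patients must be suitable for endovascular repair and have a life expectancy above 12 months, are already about 30 days past surgery, and are to be admitted promptly. On the protocol's own mortality at constant hazard, fewer than one of 77 would die while waiting, and the false-positive chance barely moves. This stands as the low end of the range. It does not remove the point: the protocol gives no expected number untreated, its word for keeping exclusions few sets no limit, and unfitness adds to deaths.

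A reader might infer several stronger things that the document does not support:

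- *That the rule affects the TEVAR arm only, so the direction is certain.* The wording covers both arms. A control patient who crosses over to early TEVAR could also be dropped as not having received the assigned treatment. If such patients are at high risk, dropping them would flatter control. The text does not say how they are handled. Refusals need not be related to prognosis.
- *That everyone without 5-year status is discarded.* Section {20c} speaks of missing primary outcome data. Under the survival methods in {20a}, a patient alive at last contact has a censored outcome, and the sentence can be read that way. The exclusion also has no fixed direction between arms.
- *That no analysis of all randomised patients will be done.* This is a condensed article and the analysis plan is not shown. One can say only that none is stated.

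**Conclusion.** The point holds as a defect in a stated rule for the primary endpoint. Pre-procedure deaths and unfitness are removed from the TEVAR arm and counted in control, so the comparison is probably tilted towards TEVAR. The tilt is certain in direction for excluded deaths taken alone, plausible for patients found unfit, and could be offset if control crossovers are dropped too.

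Its size cannot be fixed from the document. Against a nominal 2.5%, the chance of a false result favouring TEVAR runs from 2.5% (excluded patients of average risk), through about 2.6–3.2% (deaths at the protocol's own rate) and 4–7% (5–10% untreated, 60% mortality), to 7–11.5% under severe assumptions for which the protocol gives no support. The case for change does not depend on the upper end: the design expects only about 31 deaths (77×0.110 + 77×0.298 = 31.4), so two or three exclusions can decide a close result, and the one stated sensitivity analysis would not show it. The missing-outcome wording is a lesser matter of clarity.

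**What to change.** Replace the sentence in {20c} with a primary set of all randomised patients, analysed in the arm allocated whatever treatment was received, with time from randomisation to death and censoring at the date last known alive. State that control patients who receive early TEVAR stay in the control arm for this analysis. Keep the modified intention-to-treat and per-protocol sets as sensitivity analyses, and report by arm the number excluded from each, the reasons, and the deaths among them.

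One detail needs settling at the same time. Visits are timed from open surgery and end at 60 months, while randomisation comes at least about 30 days later, so the last visit falls at roughly 59 months or less from randomisation. Either let censoring at last contact handle this or add a vital-status contact at five years from randomisation, and state the 5-year horizon accordingly.

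The cost is one paragraph, taken through the amendment route in {25}, plus at most one short contact per surviving patient. The sample size stays at 154. No interim analysis is planned and recruitment was expected to run to the end of 2023, so five-year outcomes fall well after that and the change can precede the primary analysis. Patients already withdrawn before treatment should have their vital status followed as far as their consent allows.
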